#### **3.5.1 Measures obtained from the journal**

- Existing available data from lung function test.
- Home-oxygen therapy
- Prescribed medication
- Gender
- Age
- Marital status
- Smoking status
- Body mass index (otherwise measured)
- COPD classification GOLD 1-4 and A-D
- If heart failure classified by NYHA I-IV

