**3.6.1 Statistical analyses plan**

Analyses of the outcomes will be performed by the trial statistician ([name]) who is blinded to the treatment allocations. Secondary analyses will be performed by Postdoctoral fellow, PhD [name].

Baseline data will be reported as averages and standard deviations (medians and interquartile ranges) or frequencies and proportions as appropriate. Data analyses of both primary and secondary endpoints will be performed using intention-to-treat analyses. Additionally, per-protocol analyses including patients who complete  $\geq 70\%$  of the PTR and HPR rehabilitation program will be performed. Reporting will follow the CONSORT (Consolidated Standards of Reporting Trials) Statement for non-pharmacologic trials. Differences between the groups' changes of primary and secondary outcomes (10-weeks from baseline; 35-weeks from baseline and 75-weeks from baseline) will be analyzed by mixed effect models. The models include adjustment for treatment groups, age, sex, BMI, FEV1, Charlson Comorbidity Index and smoking status, and a random effect recruitment site. To account for possible regression to the mean effect, the baseline measure for the outcome will be included as a fixed effect variable in the models. Normal distribution of the model residuals is evaluated by inspection of Q-Q plots. All data are considered missing at random and because of this, the ignorability assumption for the likelihood estimator is used to account for missing data. The number of used datasets will be transparent. Survival are visualized by Kaplan-Meier curves. Group differences on number of patients being adherent, hospitalization and death are analyzed using chi-squared test. No interim analysis will be made. Statistical analyses are carried out using R 3.2.2 (R Foundation for Statistical Computing, Vienna, Austria). P-values of less than 0.05 are considered statistically significant.

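### Likelihood ignorability is claimed for all missing data, but the model conditions on baseline and analyses change, so follow-up from patients lacking a baseline (chiefly for the 6MWT) is lost

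*Protocol*

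**What the plan says.** Section 3.6.1 gives one rule for missing data. It takes every value to be missing at random, and for that reason "the ignorability assumption for the likelihood estimator is used to account for missing data". Between-group differences in change from baseline at weeks 10, 35 and 75 "will be analyzed by mixed effect models". The adjustment set is given as "The models include adjustment for treatment groups, age, sex, BMI", then FEV1, "Charlson Comorbidity Index and smoking status, and a random effect recruitment site". In addition, "the baseline measure for the outcome will be included as a fixed effect variable in the models". The analysis population is stated too: "Data analyses of both primary and secondary endpoints will be performed using intention-to-treat analyses". The section promises to show how many datasets were used. It names no other method for incomplete data.

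Three other places bear on the point. Section 5.2 offers assessments at the patient's home or a local hospital, as the patient prefers. Appendices 2, item 2 (in Danish), says that the 6MWT is done only in patients who choose to be examined at the hospitals. Table 1 schedules the 6MWT at all four visits, and Table 2 gives it an anticipated power of 0.83.

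**The concern.** A likelihood-based mixed model that conditions on covariates specifies the distribution of the response given those covariates. Under missing at random, an incomplete response can be ignored. A missing value of something the model conditions on is a different matter: the patient's likelihood contribution is undefined, and ordinary fitting leaves the patient out. Using change as the response makes this plainer, because without a baseline there is no change to analyse. The sentence in section 3.6.1 claims the method for all data, and the model described in the same section cannot deliver that.

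At stake are follow-up measurements that the trial has paid for and the patient has provided, and an intention-to-treat analysis of secondary outcomes that omits some randomised patients for a reason unrelated to follow-up. The population is defined by difficulty in reaching centre-based care, so a choice of home assessment at baseline is realistic.

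**Working it through.** The Protocol gives no figure for missing baselines, so there is none to reproduce. The check has three parts.

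**1. Which variables can be missing at baseline?**
- Section 3.6.2: randomisation follows completion of the study assessments, so CAT at baseline should be present.
- FEV1: needed for eligibility (section 3.4.1).
- Age, sex, smoking status: taken from the journal (section 3.5.1).
- BMI: taken from the journal, otherwise measured (section 3.5.1).
- Charlson index: from the national registry (section 3.5.2).
- 6MWT: hospital examinations only (Appendices 2), with home visits allowed (section 5.2). A baseline can be absent by design.

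| 6MWT setting at baseline | 6MWT setting later | Effect under the plan |
|---|---|---|
| Hospital | Hospital | Analysed |
| Hospital | Home | Missing follow-up; ignorability applies |
| Home | Hospital | Follow-up exists but is lost |
| Home | Home | No 6MWT data; nothing to recover |

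The third row is the point.

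**2. Does the model drop such patients?** In a simulated trial of 185 patients with every outcome observed, 9 baseline values and 9 BMI values were deleted, in different patients. The mixed model used 185 − 18 = 167 patients. BMI served only to show the mechanism.

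**3. What does it cost?** Inputs from the Protocol: 56 versus 36 analysed (section 3.6); hypothesised difference/SD of 26/44.5 for the 6MWT, d = 0.584, and 1100/2262 for steps, d = 0.486 (Table 2). Assumptions: the Table 2 SD is the SD of the follow-up value; baseline-to-follow-up correlation ρ is 0.3, 0.5 or 0.7; a share p of baselines is missing equally in all arms; the test is two-sided at 5%.

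The standard error factor is √(1/56 + 1/36) = 0.2136. Approximate power is Φ(λ − 1.96), with
- dropped: λ = d·√(1 − p) / [√(1 − ρ²) · 0.2136]
- kept (pooled mean plus indicator): λ = d / [√((1 − p)(1 − ρ²) + p) · 0.2136]

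For the 6MWT with ρ = 0.3 and p = 0.20:
- dropped: 0.584 × 0.894 / (0.954 × 0.2136) = 2.56, power 0.73
- kept: 0.584 / (0.963 × 0.2136) = 2.84, power 0.81

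Simulation (20,000 trials per setting, linear model on arm and baseline) gave, in percent, dropped then kept:

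| Outcome | ρ | 5% missing | 10% missing | 20% missing |
|---|---|---|---|---|
| Steps | 0.3 | 62.5 / 64.3 | 60.2 / 63.8 | 55.3 / 63.8 |
| Steps | 0.5 | 70.8 / 72.3 | 69.2 / 71.9 | 62.4 / 69.6 |
| 6MWT | 0.3 | – | – | 71.0 / 79.5 |
| 6MWT | 0.5 | – | – | 78.7 / 84.7 |

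At ρ = 0.7 the gain for steps is 0.2 to 1.9 points over the same range. The gains at 20% listed here are 6.0 to 8.5 points; repeat runs widen this to about 6 to 10. The type I error stays at its nominal level when the patients are kept. Steps serve only as a second effect size, since the Protocol gives no reason for their baselines to be missing.

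**The case against.** The best objection is that a rule for missing covariate values is ordinary SAP content, and that the Protocol nowhere says such patients are excluded. Both are true, and the absence of a rule would be no finding. What stands is narrower: the Protocol makes a positive claim that one method accounts for all missing data, and the model it fixes does not support that claim.

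A second objection is that a patient without a baseline has no change score, so no outcome is being discarded. As the response is defined, that is right. The measured follow-up value exists all the same, and it goes unused only because of that definition.

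A third is that the affected group is small. Only patients who move from home to hospital count, and the Protocol gives no number for them. That also stands and keeps the point minor. Showing how many datasets were used discloses the loss but does not recover it.

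A reader might infer more than the documents support:
- **That the six other covariates will remove patients from the primary analysis.** The entry "Existing available data from lung function test" in section 3.5.1 could suggest missing FEV1, but a patient without FEV1 cannot meet the eligibility criterion, and the other five have a stated source.
- **That the comparison is biased or intention-to-treat is broken.** Whether a baseline exists is settled before randomisation, so leaving those patients out keeps the arms comparable and costs precision.
- **That accelerometer failures will add missing baselines.** The Protocol says nothing of the kind and schedules the device at every visit.

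**Conclusion.** The point holds in a limited form. The ignorability sentence in section 3.6.1 claims too much: it covers missing follow-up, not a missing baseline that the model conditions on and from which change is computed. CAT is essentially unaffected. The practical consequence is confined to secondary outcomes whose baseline can be absent, and the 6MWT is the one for which the Protocol's own procedures make that happen.

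The loss is precision: about 0 to 2 power points with 5% of baselines missing and about 6 to 10 with 20%, for correlations of 0.3 to 0.5, and no more than about 2 points at 0.7. The missing shares and correlations are assumptions. The calculation also treats every patient without a baseline as having follow-up. For the 6MWT, those assessed at home throughout cannot be recovered under any method, so the gain depends on how many change setting. Keeping those who change rests on the missing-at-random assumption that the Protocol already makes. This is an inexpensive improvement and does not threaten the primary conclusion.

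**What to change.** In section 3.6.1, limit the ignorability sentence to missing outcome values, and state that patients with follow-up but no baseline stay in the analysis by one of two routes:

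1. Enter the baseline measurement as one of the repeated outcomes, with a baseline mean common to all arms. This handles a missing baseline within the likelihood, so the ignorability argument then applies to it.
2. Use the follow-up value, not the change, as the response. Fill a missing baseline with the mean pooled over arms and add a missing-baseline indicator. This route fails if change remains the response, because the filled value would then enter the outcome itself.

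With complete baselines, analysing the follow-up value or the change gives the same treatment estimate once baseline is a covariate, and the first route leaves it essentially unchanged. The cost is one or two sentences and a few lines of code, with no extra data. Table 1 and Appendices 2 should also be reconciled on whether the 6MWT is expected at every visit for every patient.

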### **2.1.3 Aims for the overall research project**

1. To investigate equivalent effect of HPR and PTR and superiority to CON on patient-reported health parameters such as quality of life, anxiety-depression symptoms, sleep quality, fatigue, muscular-skeletal pain, physical activity and functioning level (**RCT- study I**) (**table 2**).
2. Monitor and retrieve number of hospital admissions, length of stay and mortality from baseline throughout the follow-up period through the National Health Data Authorities (**RCT- study I**).
3. To investigate adherence to and effect from an exercise maintenance-program (similar healthcare-technologies) on self-reported health parameters of quality of life, anxiety-depression symptoms, sleep quality, fatigue, muscular-skeletal pain, physical activity and functioning level (**Maintenance - study II**).

4. Qualitatively investigate the participant experience with the intervention and maintenance program and its impact on their everyday life involving social, structural, cultural and gender factors with the following aims.

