#### **3.5.2 Measures obtained from the National Health Data Authorities at 75-weeks follow-up**

- Length of hospital stay.
- Number readmissions
- Mortality
- Any other received rehabilitation from inclusion (visit 0) to final assessment (visit 3) 75-weeks follow-up.

- Charlson comorbidity index

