***Please read appendix 1. for information on the test procedure from the physical functioning test (Danish)***

## **3.6 Sample size and statistics**

*(performed by biostatistician [name], Clinical Research Centre, University Hospital Hvidovre)*

Three primary pairwise comparisons are made in the study, equivalence test between the two interventions and the superiority test for each intervention compared to the control group for the primary outcome of respiratory symptoms (COPD assessment test). Sample size estimation for the equivalence is based on a t-test with equivalence margin of -2.5 to 2.5 (clinically relevant difference), standard deviation (SD) of 4.5, power of 80% and significance level of 5%, and estimated 56 patients necessary in each group. For both, superiority tests a minimal clinical difference of 2.5, SD of 4.5, power of 80% and significance level of 5% were used in a two-sample t-test, with fixed sample of 56 patients in the intervention groups. This yields a necessary size of 36 patients in the control group. The sample size is increased by 25% in each group to account for expected withdrawal and loss of power from adjustment and thus a total of 185 (70/70/45) patients. Power estimations for all secondary outcomes are based on the decided inclusion of 185 patients, expected standard deviation and established minimal clinical important difference (MCID) (**Table 2**).

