| Data registrations and
expense indicators | Adherence to intervention/self-maintenance   |                                                                          | X                                 | X                      | X                      |
|                                              | Adverse events recorded                      |                                                                          | X                                 | X                      | X                      |
|                                              | Number of hospital admission                 | past 12-mo                                                               | X                                 | X                      | X                      |
|                                              | Length of stay – hospital admission          | past 12-mo                                                               | X                                 | X                      | X                      |
|                                              | Consultant visits                            | past 12-mo                                                               | X                                 | X                      | X                      |
|                                              | Mortality                                    |                                                                          | X                                 | X                      | X                      |
|                                              | Comorbidities                                | X                                                                        | X                                 | X                      | X                      |
| Descriptive variable                  |                                              |                                                                          |                                   |                        |                        |
| Lung function test                           | FEV1/FVC ratio in %                          | X                                                                        |                                   |                        | X                      |

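### Hospital admissions are recorded as counts with a prior-year value, but the only test named for them is an unadjusted chi-squared test on numbers of patients

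*Protocol*

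**What the plan says.** Aim 2 in section 2.1.3, assigned to RCT study I, is to "Monitor and retrieve number of hospital admissions, length of stay and mortality from baseline throughout the follow-up period". Table 1 (under Outcomes) has a row "Number of hospital admission", filled at weeks 10, 35 and 75, with a baseline entry for the past 12 months. Section 3.5.2 adds register data at 75 weeks, including "Number readmissions".

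For the analysis, section 3.6.1 states: "Group differences on number of patients being adherent, hospitalization and death are analyzed using chi-squared test". The same section uses mixed models for the primary and secondary outcomes and says that "the baseline measure for the outcome will be included as a fixed effect variable in the models". No such adjustment is stated for the chi-squared comparisons, and no count or rate model appears anywhere. For death, "Survival are visualized by Kaplan-Meier curves"; the test is again chi-squared. The threshold is "P-values of less than 0.05 are considered statistically significant", with no statement of one or two sides.

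**The concern.** The data are a count per patient over 75 weeks, with a pre-trial value of the same count. The named test works on numbers of patients, so someone admitted once and someone admitted five times contribute the same. It also makes no use of the prior-year count, which is likely to predict later admissions. The chi-squared test is valid for the question of admitted or not, but that is a narrower question than the number of admissions in Aim 2.

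At stake is a comparison that is already weak at this sample size and is made weaker by the choice of test, although the variables for a better analysis are already planned for collection.

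**Working it through.** **Plan's own figure.** There is none to reproduce: Table 2 has no row for admissions or death. The group sizes are taken as stated, "thus a total of 185 (70/70/45) patients", so each intervention is compared with control as 70 v 45.

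**Inputs.** From the protocol: 70 v 45, follow-up T = 75/52 = 1.44 years, alpha 0.05 (taken as two-sided). Assumed, because the protocol gives none: control rate 0.4, 0.8 or 1.2 admissions per year; negative binomial dispersion k of 1 or 2; rate ratio 0.6; full register follow-up.

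**Formulas, worked for 0.8 per year and k = 1.**
- Mean counts: m0 = 0.8 × 1.4423 = 1.154; m1 = 0.6 × 1.154 = 0.692.
- Probability of any admission, 1 − (1 + k·m)^(−1/k): p0 = 0.536, p1 = 0.409, pooled 0.459.
- Chi-squared: standard error 0.0952 under the null and 0.0948 under the alternative, so power = Φ((0.127 − 1.96 × 0.0952)/0.0948) = Φ(−0.63) = 0.26.
- Negative binomial: Var(log RR) = (1/m0 + k)/45 + (1/m1 + k)/70 = 0.0415 + 0.0349 = 0.0764, standard error 0.276. Power = Φ(0.511/0.276 − 1.96) = Φ(−0.11) = 0.46.
- With the prior-year count, if each patient's underlying risk persists fully, k falls to about k/(1 + k × rate) = 1/1.8 = 0.556. The variance becomes 0.0602, the standard error 0.245, and power = Φ(2.08 − 1.96) = 0.55.

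**Simulation.** Gamma-frailty Poisson counts, 1000 runs per cell (Monte Carlo standard error at most √(0.25/1000) = 0.016). Ranges cover 50% to 100% persistence of patient risk from the prior year.

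| Control rate/yr | k | Chi-squared | Neg. binomial | + prior-year count |
|---|---|---|---|---|
| 0.4 | 1 | 0.24–0.26 | 0.30–0.34 | 0.31–0.36 |
| 0.4 | 2 | 0.19–0.20 | 0.26–0.27 | 0.28–0.31 |
| 0.8 | 1 | 0.27 | 0.45 | 0.47–0.52 |
| 0.8 | 2 | 0.18 | 0.31–0.32 | 0.35–0.45 |
| 1.2 | 1 | 0.25–0.26 | 0.51–0.53 | 0.53–0.66 |
| 1.2 | 2 | 0.18 | 0.36–0.39 | 0.40–0.58 |

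A second simulation at 75% persistence gave 0.18–0.28, 0.25–0.52 and 0.26–0.56 for the three analyses. The count alone adds about 6–8 points at 0.4 per year and 13–28 points at 0.8–1.2. The prior-year covariate adds a further 1 to 19 points, most when patients differ strongly and persistently.

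**Type I error.** With rate ratio 1, rejection rates were 0.03–0.07 for chi-squared and the unadjusted count model, and 0.05–0.075 for the adjusted one. A small part of the adjusted gain is therefore test size.

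**Sensitivity (analytic).**
- Rate ratio 0.7, 0.8 per year, k = 1: 0.15, 0.26 and 0.32.
- k = 0.5, 1.2 per year, rate ratio 0.6: 0.35, 0.67 and 0.75.
- 10 weeks: chi-squared 0.10–0.17, count model 0.09–0.18, so no gain.

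**Death.** For 10% v 5% mortality with proportional hazards: hazard ratio = ln 0.95/ln 0.90 = 0.487; expected deaths 4.5 + 3.5 = 8; log-rank power = Φ(0.720 × √(8 × 0.391 × 0.609) − 1.96) = 0.17, against 0.19 for chi-squared. At 15% v 8% the figures are 0.21 and 0.23; at 20% v 10%, 0.31 and 0.34. Chi-squared gives up nothing.

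**The case against.** - **Aim 2 carries no hypothesis.** It is a monitoring aim. Superiority and equivalence are claimed in Aim 1, and Table 1 files admissions with data registrations and expense indicators. This stands: the point concerns a descriptive or secondary comparison, not a powered one. It does not remove the mismatch, because section 3.6.1 does name a test for group differences.
- **Details may sit in the statistical analysis plan, or admissions may fall under the mixed models.** The second reading is arguable, with chi-squared covering only the proportion hospitalised. But section 3.6.1 singles out hospitalisation for chi-squared, and mixed models checked by Q-Q plots of residuals suit a skewed count with many zeros poorly. The protocol has not left the method open.
- **The size rests on assumed rates.** It does, and the gain is modest at 0.4 per year. A sustained rate ratio of 0.6 may also be optimistic: Appendices 1 offers controls the maintenance programme after week 10, that is for 65 of the 75 weeks, while section 3.7.3 says they are offered no intervention. Those passages must be reconciled.
- **The proportion hospitalised is a legitimate quantity** that frequent attenders do not dominate. Agreed, and a reason to keep it alongside the count.

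A reader might infer that the death comparison loses power in the same way. It does not: death is one event per patient with no baseline counterpart, and the calculation shows no loss. Expected deaths in 45 controls would be 0.9, 2.3 and 4.5 at assumed mortality of 2%, 5% and 10%, so the chi-squared approximation could be rough if deaths are few. That calls for an exact test, and is not a power argument.

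**Conclusion.** The concern holds for number of admissions over 75 weeks. The only named test discards repeat admissions, and no use of the prior-year count is stated. For 70 v 45 and a rate ratio of 0.6, with control rates of 0.4 to 1.2 per year and dispersion 1 to 2, power is about 0.18–0.28 for chi-squared, 0.25–0.53 for a negative binomial model and 0.26–0.66 with the prior-year covariate. Rates, dispersion and effect are assumptions, not protocol figures.

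It would be wrong to conclude that the change makes this a well-powered comparison. No scenario examined reaches 80%, the gain is nil at 10 weeks, and it shrinks with a weaker effect. Nor is the chi-squared test invalid. No power claim is made for death, and no model is recommended for total bed-days, where none was tested. The primary outcome is unaffected.

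**What to change.** In section 3.6.1 or the statistical analysis plan, before the data are analysed:

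- Analyse number of admissions to week 75 by negative binomial regression, with log time alive as offset, treatment arm, and past-12-month admissions as covariate. Fix the coding of that covariate in advance.
- Keep the proportion hospitalised, with its chi-squared test, as a supportive figure.
- For death, report a log-rank or Cox estimate beside the planned Kaplan-Meier curves, or an exact test if events are few.

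The cost is wording and a few lines of code; the counts, the prior-year value and mortality are already collected. The drawback is some dependence on the model and a slightly liberal test in samples of this size, so check the result with robust or bootstrap standard errors. The offset accounts for time at risk but does not fully deal with death as an event that ends follow-up, so report deaths by arm next to the admission rates.
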